## **7.2 Assessment of Safety**

The safety of the study medication will be assessed by recording the adverse events occurring during the entire course of the study, as mentioned in detail in “Adverse Events” section of the protocol. All observed (during general and physical examination of patients or in the laboratory parameters) or volunteered adverse events regardless of suspected causal relationship to the study test product will be recorded on the adverse event page of the CRF. ECG of all the patients will be done at the screening and at the end of the study.

|                                                                                  |                                                                                                       |                                                              |
|----------------------------------------------------------------------------------|-------------------------------------------------------------------------------------------------------|--------------------------------------------------------------|
| [figure not shown] | Clinical trial to evaluate efficacy and safety of Amla Extract (AMX160) in patients with Dyslipidemia | Project No. AN-03ASE
0115H2-SYN02
Ver.01, Dt: 01-01-15 |
|----------------------------------------------------------------------------------|-------------------------------------------------------------------------------------------------------|--------------------------------------------------------------|

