### Overall tolerability evaluation:

The overall tolerability to study medication will be evaluated at the end of study as per the following criteria:

| Grade     | Description                                                                                                                       |
|-----------|-----------------------------------------------------------------------------------------------------------------------------------|
| Excellent | No adverse event                                                                                                                  |
| Good      | Mild adverse event(s) reported which subsided with or without medication and did not necessitate stoppage of study medication     |
| Fair      | Moderate adverse event(s) reported which subsided with or without medication and did not necessitate stoppage of study medication |
| Poor      | Severe or serious adverse event(s) which necessitated stoppage of study medication                                                |

The safety endpoints would be:

- Local and systemic adverse events reported during the study
- Serious adverse events reported during the study
- Overall tolerability evaluation at the end of study

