not be included in the Per Protocol efficacy analysis while all the patients (including those with deviations and violations) will be considered for modified Intention To Treat efficacy analysis if they have completed visit 3 (week 4) with laboratory evaluation. All the subjects who have been dispensed study medication and have completed visit 3 (week 4) will be considered for safety evaluation.

Neither the investigator nor Arjuna Natural Extracts Limited will alter this study protocol. Amendments should be made only in exceptional cases once the study has started. Any change in the protocol should be approved by IEC / IRB, wherever necessary before implementation.

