### 10.2.2 Adverse Events Recording

Adverse events will be elicited using the open question - Have you noticed any change in your health since your last visit? Events involving adverse drug reactions, illnesses with onset during the study or exacerbation of pre-existing illnesses should be recorded.

All observed or volunteered adverse events regardless of treatment group or suspected causal relationship to the study test products will be recorded on the adverse event page of the CRF. Safety data including adverse events will be tabulated for clinical review.

For all adverse events, the Investigator must pursue and obtain information adequate both to determine the outcome of the adverse event and to assess whether it meets the criteria for classification of a serious adverse event requiring immediate notification to the Sponsor's representative / medical expert.

Follow-up of the adverse event, even after the date of therapy discontinuation, is required if the adverse event or its sequel persist. Follow-up is required until the event or its sequel resolve or stabilises at a level acceptable to the Investigator and the study monitor.

|                                                                                  |                                                                                                       |                                                              |
|----------------------------------------------------------------------------------|-------------------------------------------------------------------------------------------------------|--------------------------------------------------------------|
| [figure not shown] | Clinical trial to evaluate efficacy and safety of Amla Extract (AMX160) in patients with Dyslipidemia | Project No. AN-03ASE
0115H2-SYN02
Ver.01, Dt: 01-01-15 |
|----------------------------------------------------------------------------------|-------------------------------------------------------------------------------------------------------|--------------------------------------------------------------|

All the adverse events will be documented in the respective CRFs including

1. Type of adverse event
2. Date of onset
3. Severity
4. Treatment given
5. Association or relationship to the study medication
6. Date of resolution
7. Duration
8. Outcome
9. Whether the adverse event is serious or not

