#### Discontinuation of the study due to Adverse Events

The reason for a subject discontinuing from the study will be recorded in the CRF. A discontinuation occurs when an enrolled subject ceases participation in the study, regardless of the circumstances, prior to the completion of the study. A discontinuation must be reported immediately to the sponsor if it is due to a serious adverse event. The final evaluation as required by the Protocol will be performed at the time of study test product discontinuation if medically acceptable or as soon as possible after that. The Investigator will record the reason for study discontinuation and, if possible, provide or arrange for appropriate follow-up and document the cause of the subject's condition.

The association of the adverse events to the study medication can be ascertained by WHO criteria as mentioned below:

| Causality term              | Assessment criteria*                                                                                                                                                                                                                                                                                                                                                                                                                                                                                          |
|-----------------------------|---------------------------------------------------------------------------------------------------------------------------------------------------------------------------------------------------------------------------------------------------------------------------------------------------------------------------------------------------------------------------------------------------------------------------------------------------------------------------------------------------------------|
| Certain              | 
 
• Event or laboratory test abnormality, with plausible time relationship to test product intake
 
• Cannot be explained by disease or other drugs
 
• Response to withdrawal plausible (pharmacologically, pathologically)
 
• Event definitive pharmacologically or phenomenologically (i.e. an objective and specific medical disorder or a recognized pharmacological phenomenon)
 
• Rechallenge satisfactory, if necessary
 
 |

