##### 14.4.2 Safety Population

Safety population will include all the randomized patients who have been dispensed study medication and have completed at least one post randomization visit i.e. visit 3 (week 4) will be considered for safety evaluation.

|                                                                                   |                                                                                                       |                                                              |
|-----------------------------------------------------------------------------------|-------------------------------------------------------------------------------------------------------|--------------------------------------------------------------|
| [figure not shown] | Clinical trial to evaluate efficacy and safety of Amla Extract (AMX160) in patients with Dyslipidemia | Project No. AN-03ASE
0115H2-SYN02
Ver.01, Dt: 01-01-15 |
|-----------------------------------------------------------------------------------|-------------------------------------------------------------------------------------------------------|--------------------------------------------------------------|

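### The safety population is limited to patients who completed the week-4 visit, so a treated patient who leaves earlier because of an adverse event is not counted in the safety analysis

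*Protocol*

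**What the plan says.** Protocol section 14.4.2 limits the safety population to randomised patients who "have been dispensed study medication and have completed at least one post randomization visit i.e. visit 3 (week 4"). Section 8.1 sets the same condition: "All the subjects who have been dispensed study medication and have completed visit 3 (week 4) will be considered for safety evaluation". Sections 4.3 and 8 place visit 3 at day 28 with a window of 5 days either side.

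Section 7.2 describes the safety assessment as "recording the adverse events occurring during the entire course of the study". Its endpoints are adverse events, serious adverse events and an overall tolerability grade. The worst grade is "Severe or serious adverse event(s) which necessitated stoppage of study medication".

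On data collection, section 10.2.2 states: "All observed or volunteered adverse events regardless of treatment group or suspected causal relationship to the study test products will be recorded". It adds: "Safety data including adverse events will be tabulated for clinical review", without naming a population. For patients who stop because of an adverse event, the same section states: "The final evaluation as required by the Protocol will be performed at the time of study test product discontinuation". It allows a delay where an immediate evaluation would be medically unsuitable.

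**The concern.** Completing a visit about four weeks after randomisation is a post-treatment event, and it can itself depend on whether the patient was harmed. The same condition appears in the modified intention-to-treat definition (section 14.4.1). It has a purpose there, because a post-baseline lipid value is needed. It has no such purpose for safety.

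The patients it can remove include those of most interest for tolerability. Section 9.3 allows no dose modification. Under section 9.8 a patient whose code is broken in an emergency is discontinued. If either situation ends participation before visit 3, the patient leaves the safety set. The worst tolerability grade is defined by stopping medication, so it is especially exposed.

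Safety is part of the single study objective (section 3). With 49 patients per arm, losing a few such patients can change a reported rate from several per cent to zero.

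**Working it through.** **Inputs**
- 44 evaluable patients per arm and 10% dropout (section 14.1). 44 / 0.90 = 48.9, rounded up to 49 per arm and 98 in total, which agrees with the protocol.
- Dropouts are not replaced (section 8.1).
- The protocol gives no figure for the size of the safety set and no split of dropout by time or cause. The counts of early leavers below are assumptions.

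**Step 1. Who is in and who is out**

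| Patient | In the safety set? |
|---|---|
| AE in week 1, attends visit 3 | Yes, event counted |
| Stops capsules in week 1, attends visit 3 | Yes; the text requires attendance, not continued dosing |
| Takes capsules, has an AE or SAE, leaves before visit 3 | No |
| Misses visit 3, attends visit 4 or 5 | No on the strict reading; the wording is ambiguous |

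No section restores the third patient. Data on that patient would exist nonetheless, through unscheduled visits for adverse events (section 8), the recorded reason for withdrawal (section 6.3), SAE reporting and the evaluation at discontinuation (both section 10.2.2).

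**Step 2. Possible size of the set**

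All-cause dropout allowed for is 98 × 0.10 = 9.8 patients. If between 0% and 100% of these occur before visit 3, the set lies between 98 and 98 − 9.8 = 88.2, about 88. At 50% it is 98 − 4.9 = 93.1, about 93.

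**Step 3. Direction of the bias**

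Let *m* of *n* patients in an arm be lost before visit 3, with event proportion *pL* among the lost and *pR* among the retained.

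- Rate in all treated patients = [*m·pL* + (*n* − *m*)·*pR*] / *n*
- Rate reported = *pR*
- Reported minus all treated = (*m*/*n*)(*pR* − *pL*)

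The bias is downward only when *pL* exceeds *pR*. A case in the other direction: 5 of 49 leave early without an event and 5 of the remaining 44 have one. The report shows 5/44 = 11.4% against 5/49 = 10.2% in all treated patients.

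**Step 4. Illustration for AE discontinuation**

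Assume *k* of 49 active patients leave for an AE before visit 3 and no other patient stops for an AE, so *pL* = 1 and *pR* = 0. Limits are exact (Clopper-Pearson, two-sided 95%). For zero events in *N* patients the upper limit is 1 − 0.025^(1/*N*).

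| *k* (assumed) | All treated (95% CI) | Reported | Upper limit |
|---|---|---|---|
| 1 | 1/49 = 2.0% (0.1 to 10.9) | 0/48 | 7.4% |
| 3 | 3/49 = 6.1% (1.3 to 16.9) | 0/46 | 7.7% |
| 5 | 5/49 = 10.2% (3.4 to 22.2) | 0/44 | 8.0% |

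At *k* = 3 the all-treated rate is still inside the reported interval. At *k* = 5, which would need the whole 10% allowance in that arm to be early and caused by AEs, 10.2% lies above the reported upper limit of 8.0%.

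**The case against.** Several objections limit the point.

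- **Scope.** A reader might infer that early adverse events vanish from the safety analysis. They do not. An event in week 1 is counted if the patient attends visit 3. For a patient who does not attend, the event stays in the case record form and, if serious, in the SAE reports. Section 10.2.2 also tabulates safety data for clinical review with no population named. What is lost is membership of the defined safety set and the rates computed on it.
- **Tolerance.** A reader might infer that inclusion requires about four weeks of tolerated treatment. The text requires dispensing and attendance, and the window allows visit 3 as early as day 23.
- **Direction.** Downward bias is not automatic. Section 6.3 also allows withdrawal for reasons unrelated to the product, and the third step of the working shows a rate that rises.
- **Contradiction.** Section 7.2 says which events are recorded and over what period. It does not define an analysis population, so it is in tension with section 14.4.2 rather than in flat contradiction.
- **Missed visit 3.** In section 14.4.2, at least one visit can be read as a minimum that a later visit would meet. Section 8.1 favours the strict reading. The wording is ambiguous and should not be reported as a certain exclusion.
- **Size.** The 10% in section 14.1 covers all causes over 12 weeks, and section 10.1 reports no adverse events in earlier dyslipidaemia studies of the product. The early-leaver counts have no source in the protocol.

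All of these stand as limits on how far the point reaches. None of them puts back into the safety set a treated patient who leaves before visit 3 with an adverse event. Nor can the matter be left to an analysis plan, because the protocol fixes the rule in two places.

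**Conclusion.** The definition is wrong as written and should be changed before the analysis. Treated patients who leave before visit 3 are excluded from the numerators and denominators of the safety analysis, including those who leave because of an AE or SAE, although their events are recorded. AE, SAE and tolerability rates are too low to the extent that these patients have more events than those retained. That is likely where the event causes the departure, and it matters most if the two arms differ in early intolerance.

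The actual size cannot be derived from the protocol. Under the assumed counts, 6.1% becomes 0/46 and, in the extreme case, 10.2% becomes 0/44. Both rest on 49 patients in the arm, every early leaver having stopped for an AE, and no other AE discontinuation. The primary triglyceride endpoint is not affected.

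**What to change.** Change sections 8.1 and 14.4.2 together, so that both read in substance: the safety population is all randomised patients who took at least one dose of study medication, analysed by treatment received, with no requirement to have completed any visit. Patients who were dispensed medication are included unless they are known to have taken none. This also removes the ambiguity about patients who miss visit 3 and return later.

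The cost is two sentences. No visit, sample or patient is added, because the adverse events are already recorded and followed up. Reported rates may be higher than under the current rule where early leavers had events.

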### **14.4.3 Data Analysis**

The data collected from the CRFs will be analysed for demographics, efficacy & safety. Data will be presented as mean  $\pm$  SD/SE or number (percentage). Descriptive statistics will be used for different variables at baseline. *P* value of  $< 0.05$  will be considered as statistically significant. Standard statistical tests will be used to analyse the data obtained. For efficacy analysis both, modified Intention To Treat (mITT) analysis and Per Protocol (PP) analysis will be done. The PP analysis will be considered as definitive, while the mITT analysis will be considered as supportive during the trial analysis.

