### **8.1 Protocol violation, deviation, waiver or amendments**

During this study examples of deviations may include, but are not limited to:

- Participant seen outside window period ( $\pm$  5 days)
- Missed or incomplete study procedure (e.g. examination)

During this study following will be considered as protocol violations:

- Failure to report within  $\pm$  7 days
- Failure to obtain written informed consent
- Missing Informed Consent Form (ICF)
- ICF does not contain all the required signatures
- ICF used was not the current EC approved version
- Participant did not meet eligibility criterion
- Prescribed dosing outside protocol guidelines
- A breach of confidentiality
- Falsifying research or medical records
- Participant receives wrong treatment
- Randomization of participant prior to EC approval of protocol
- Subject withdrawal criteria not followed
- Use of prohibited concomitant treatments

Any deviation or violation from the Protocol should be duly explained with justification(s) thereof by the concerned investigator. The Investigator should promptly report to the Ethics Committee, sponsor's representative / medical expert, deviation / violation from the Protocol, if any which may cause immediate hazards to the subjects. There will be no protocol waiver in this study. Subjects dropped out before the study completion will not be replaced. Patients violating the Protocol will

|                                                                                  |                                                                                                       |                                                              |
|----------------------------------------------------------------------------------|-------------------------------------------------------------------------------------------------------|--------------------------------------------------------------|
| [figure not shown] | Clinical trial to evaluate efficacy and safety of Amla Extract (AMX160) in patients with Dyslipidemia | Project No. AN-03ASE
0115H2-SYN02
Ver.01, Dt: 01-01-15 |
|----------------------------------------------------------------------------------|-------------------------------------------------------------------------------------------------------|--------------------------------------------------------------|

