#### 14.3 Statistical analysis

##### 14.4.1 Immunogenicity Population

##### Per Protocol Population

All the randomized patients who will complete the trial as per the defined protocol (including deviations) with both baseline and end of the study laboratory assessments will be considered in the Per Protocol analysis.

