##### Modified Intention to Treat Population (mITT)

All the randomized patients with baseline laboratory investigations and those who have completed at least one post randomization visit i.e visit 3 (week 4) with laboratory evaluation including patients with protocol violations will be considered in the mITT analysis.

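### In a placebo-controlled superiority trial the per-protocol analysis is named definitive and mITT only supportive, so the efficacy verdict rests on patients selected after randomisation

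*Protocol*

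**What the plan says.** Section 14.4.3 fixes the order of the two efficacy analyses: "The PP analysis will be considered as definitive, while the mITT analysis will be considered as supportive during the trial analysis". No other section reverses it.

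The PP set is described in two places. The Per Protocol Population paragraph takes "All the randomized patients who will complete the trial as per the defined protocol (including deviations"), and it requires laboratory results both at baseline and at the final visit. Section 8.1 adds that patients violating the protocol will "not be included in the Per Protocol efficacy analysis while all the patients (including those with deviations and violations") go into mITT if they have week-4 laboratory data.

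The violations listed in section 8.1 include "Failure to report within" ±7 days, use of prohibited concomitant treatment, receipt of the wrong treatment and withdrawal criteria not being followed. They also include "A breach of confidentiality" and consent forms with missing signatures.

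The mITT set consists of randomised patients with baseline laboratory data who "completed at least one post randomization visit i.e visit 3 (week 4) with laboratory evaluation including patients with protocol violations".

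The primary endpoint (section 7.1) is mean percent change in TG at 12 weeks. Section 14.2 rules out imputation of missing data.

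**The concern.** This is a superiority question, although the protocol does not use that word. The design is randomised, double blind and placebo controlled (section 4.1.1). The placebo is there to show that efficacy is not a placebo effect (section 11.2). The sample size rests on a two-sided test of a difference (section 14.1), and no equivalence or non-inferiority margin appears anywhere. Section 4.4 relies on randomisation to prevent selection bias, and section 14.4.3 gives up that protection in the analysis that decides the trial.

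A patient can leave the PP set for reasons linked to treatment or response. A patient whose lipids do not improve may start a lipid-active product, which section 9.6 prohibits. A patient who tolerates the capsules poorly may fall below 80% intake, withdraw consent or be withdrawn on the investigator's judgement (section 6.3). If such exclusions differ between arms, the PP comparison can show a difference that treatment did not cause. The administrative violations do not create that bias, but they remove informative patients from the deciding analysis for reasons unrelated to week-12 TG.

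The protocol states this rule outright. It is not a detail left to an analysis plan, and a plan that follows the protocol would inherit it.

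**Working it through.** **1. The protocol's sample size.** Inputs from section 14.1: difference 51, SD 76, effect size rounded to 0.7, two-sided alpha 5%, power 90%, dropout 10%.

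- Normal approximation: n = 2(1.960 + 1.2816)² / 0.7² = 2 × 10.51 / 0.49 = 42.9, so 43 per group.
- Two-sample t-test: 43.87, so 44 per group, which matches the protocol.
- Dropout: 44 / 0.9 = 48.9, so 49 per group and 98 in total, which also matches.

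**2. What the 10% allowance covers.** It is stated for dropout only, and 49 × 0.9 = 44.1 leaves 44 per group. If dropout reaches 10% and some completers are also violators, the PP set falls below 44. Power of the t-test at the planned effect size of 0.7:

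| n per group in PP | Power |
|---|---|
| 44 | 90.1% |
| 42 | 88.7% |
| 40 | 87.1% |

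**3. Which patients the ordering affects.** A patient without a week-12 TG value cannot be in PP. With no imputation, that patient also contributes nothing to an observed-case week-12 comparison in mITT. On that reading the two analyses differ mainly in the completers who committed a violation. The protocol gives no expected number for them.

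**4. Illustration of bias.** Assumptions, none of them from the documents: no true effect; normal outcomes; 49 per arm; k patients excluded from the active arm in relation to poor outcome; k patients removed at random from placebo; two-sided t-test at 5%. In the worst case the k poorest responders are removed. In the milder case the excluded patients are the k worst on a variable that correlates 0.5 with outcome. Results by simulation:

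| k excluded per arm | Type I error, correlation 0.5 | Type I error, worst case |
|---|---|---|
| 1 | about 5% | about 6% |
| 2 | about 6% | about 8% |
| 3 | about 6% | 10% to 11% |
| 5 | about 8% | about 17% |

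With k = 5 the active mean shifts by about 0.10 SD (correlation 0.5) or 0.19 SD (worst case). If the same mechanism removes 5 patients from both arms, there is no mean bias; rejection is then between 5% and 6%, or between 8% and 9% in the worst case.

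**The case against.** The strongest reply is that the ordering itself may do little harm. The trial is double blind, so investigators and patients cannot select knowingly by arm. Section 6.3 has no explicit lack-of-efficacy withdrawal criterion. Deviations, including visits outside ±5 days, stay in PP; lateness removes a patient only beyond ±7 days. Patients without week-12 data are lost to an observed-case mITT comparison as well. All of this stands, and it limits the likely size of the problem. It does not remove it: blinding does not stop exclusion from following tolerability or response, and one-arm asymmetry remains possible.

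A second reply is that mITT is no clean alternative, because it requires a completed week-4 visit with laboratory data and so is also selected after randomisation. This is correct. Swapping the two labels would not be enough.

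Three stronger readings are tempting, and the documents do not support them:

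- **A false-positive rate near 17%.** That figure needs the five poorest responders, and only those on active treatment, to be excluded. Five is about the whole dropout allowance (10% of 49), and most dropouts would be missing from a week-12 mITT comparison too.
- **A definitive set certain to fall below 44 per group.** It falls below only if dropout reaches 10% and there are also violators among completers.
- **A bias in mg/dL.** Section 14.1 gives no unit for 51 and 76, and the primary endpoint is percent change, so multiplying an SD shift by 76 does not give bias on that endpoint.

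Power should also be read at 0.7. At the unrounded 51/76 = 0.671, 44 per group already gives only 87.5%. That is a consequence of rounding the effect size and is a separate matter.

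**Conclusion.** The point holds. The protocol assigns the efficacy verdict to a post-randomisation subset in a superiority trial, and nothing in it justifies or reverses that order. The defect does not depend on a particular bias estimate, and the documents supply none, because they give neither the expected number of violators nor any link between violation and outcome.

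For the few violating completers that the ordering is likely to remove, the illustration in the working points to a modest excess over 5%, and to more only under worst-case selection in one arm. If more patients are affected, or selection is stronger, the excess grows. The conditional loss of power at the planned effect size is 1.4 points (90.1% to 88.7%) with 42 per group or 3.0 points (90.1% to 87.1%) with 40.

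The point still needs correcting because it governs the conclusion on the primary endpoint, and because changing the definitive set after unblinding would not be credible.

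**What to change.** Before unblinding:

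1. In section 14.4.3, make the analysis of randomised patients in their assigned group, violators included, definitive for the primary endpoint. Make PP supportive.
2. Define that set. Either use all randomised patients, or keep mITT and justify its week-4 laboratory requirement.
3. For the primary endpoint, replace the no-imputation rule in section 14.2 with a stated approach to missing week-12 values. One option is a likelihood-based repeated-measures model using the week 4, 8 and 12 TG values already scheduled. Patients with no TG value after randomisation should be counted and reported by arm.
4. Limit PP exclusions to violations that can plausibly affect week-12 lipids, and list them before unblinding. Breach of confidentiality and consent-form signatures would then be handled as conduct matters, not as reasons to leave the PP efficacy set.

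The cost is edits to the population, missing-data and hierarchy text, with matching wording in any analysis plan. No new patients or assessments are needed. The estimated effect may be somewhat smaller than under PP.
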